#### 3.4.2 Pharmacokinetics for GM1

Pharmacokinetics (PK) of GM1 has been studied in various set-ups. This is complicated by the fact that GM1 can be also synthesized/catabolised by the body. One study using radiolabelled GM1 showed that after i.v. injection, 90% of circulating GM1 is removed before 10 h and that it accumulates first in liver and second in the brain of rats. In humans, the endogenous blood concentration is in the range of 100 ng/ml therefore not affecting measurements when 100, 200 or 300 mg were injected i.v. as a single bolus. In this study, the PK analysis done by non-compartmental analysis showed a bi-phasic decrease, a relatively long mean resident time (43 h) and a very low clearance (below 3 ml/min). This means that GM1 is almost exclusively metabolised and either used in cells or further degraded. Finally, blood concentration of GM1 has been studied after i.m or s.c administration allowing a longer half-life in the blood which was postulated to obtain longer circulation time to increase brain delivery. Indeed, when injected s.c. the delivery is delayed and the peak in blood reached after a couple of days. Interestingly, even if GM1 presents a rather long life in blood, the most successful studies used daily or even bi-daily GM1 injections to maintain high levels of GM1 in blood. This might be a pre-requisite for free GM1 to “pass” the blood brain barrier. PK of lipids cannot be analysed like small molecules or other active substances. In addition, liposomal formulations have a PK that is mainly driven by the liposome shell and less dependent from the API (inside). Clinical studies in humans are therefore necessary in order to understand the PK of TLN.

#### 3.4.3 Clinical safety of GM1

The clinical tolerability profile of GM1 is extremely positive. So far, there are no indications of acute or long-term cumulative toxicity. Intravenous single doses of 2500 mg GM1 showed no acute clinical side effects. The repeated parenteral administration of high doses of GM1 (up to 2500 mg/day on 5 days per week each) resulted in increased cholesterol and triglyceride levels and an increase in

apolipoprotein B in healthy volunteers after 4 weeks. All changes were regredient after treatment was stopped. Apart from the above-mentioned laboratory readouts changes, no other effects were observed. Over the total of the above mentioned 51 clinical studies the AEs reported are local pain during i.m. injections, rash and other skin reactions, exfoliative dermatitis, severe allergic reaction in one patient, hyperlipidaemia without a clear causal relationship to GM1. Furthermore, these AEs were only observed sporadically and inconsistently. Among all of the patients, one patient developed a symptom consistent with Guillain-Barré syndrome (GBS). This patient suffered a stroke before treatment with GM1 and had a long medical history including alcohol abuse, atrial fibrillation, congestive heart failure, angina, liver insufficiency, diabetes and chronic symmetric sensory neuropathy. The most reproducible AEs during long-term treatment of PD patients so far were found with 100 mg b.i.d. GM1 s.c. over a period of 2.5 to 5 years and were limited to local injection reactions such as redness and swelling.

The GBS is the only potential severe adverse effect discussed in the context of GM1. In the 1980s, ganglioside mixtures of bovine origin were used for the treatment of various neurological conditions in several European countries, especially in Italy and Spain. Following a number of GBS associated with ganglioside-mixture-treatments, the corresponding products were withdrawn from the European market in the early 1990s. Noteworthy, this withdrawal coincided in Europe with the peak time of bovine spongiform encephalopathy (BSE) through a newly discovered type of infection caused by prions, raising scrutiny for any human use of products derived from bovine brain. Meanwhile, bovine-free ganglioside products were developed from porcine brain material. BSE has never been documented in pigs and is almost eradicated in 2019, limiting the potential for a spread across species. Neither epidemiological studies nor post-marketing safety data in over 1 million patients exposed to a GM1-product from porcine brain worldwide support the incidence of GBS to be associated with GM1 use. Additionally, the injection of GM1 alone had no immune-stimulating effects and no anti-GM1 antibodies were detected after long-term treatment with GM1 doses of 1000 mg intravenous followed by 200 mg/day s.c. for 18 weeks. GM1 derived from pigs, manufactured by TRB Chemedica, remains in clinical use as a mono-substance in several countries.

#### 3.4.4 Clinical safety of TLN's excipients

Eventual excessive cholesterol or sphingomyelin enrichment are expected to be identified through collected lab values and should be reversible once the dose is lowered or treatment is suspended. In the routine lab analyses, liver enzymes will be monitored. Provided no enzymatic deficiencies like lipid storage disorders (e.g., gangliosidosis) are present, which would lead to a study exclusion in the first place, all molecules of TLN will enter the natural turnover of the respective molecular species. A 30 mL vial of TLN contains 180 mg of liposomal GM1; [REDACTED]

[REDACTED]. The USFDA recommends a maximum dose of 300 mg of cholesterol daily, while no recommendation exists for sphingomyelin, daily dietary uptake of sphingolipids is evaluated at 400 mg. Use of TLN could then be compared to dietary uptake of these lipids. At the maximum planned dose of TLN, [REDACTED] will be injected, compared to weekly dietary uptake and/or recommended dose (2800 and 2100 mg respectively) both excipients remain in the range of a weekly dietary consumption and should not overly imbalance these two metabolites.

#### 3.4.5 Products containing the API GM1 currently marketed worldwide

The manufacturer TRB Chemedica is authorized to provide GM1 under the name Sygen in Brazil, Sinaxial in Argentina and Shijieyin in China. The dose administration varies from 20 to 100 mg daily in i.m. or i.v. injections. The indications are initial or early stages of traumatic, acute vascular lesions of the central nervous system (brain and spinal cord), peripheral neuropathies and PD.

### 3.5 Dose Rationale

Four publications are used as reference points for the dose rationale of this trial.

- 1- Best efficacy results in PD patients were achieved by Schneider *et. al.* in 2013 in a controlled/randomized trial setting with a daily dose of 100 mg *b.i.d.* via s.c. injections over a period of 2.5 years.
- 2- The highest dose given to humans was in a trial published by Roberts *et. al.* in 1993 where healthy volunteers received a daily dose of 2500 mg daily 5/7 days via i.v. injection for 6 weeks.
- 3- Treatment with GM1 via direct infusion into the brain was performed in patients suffering from Alzheimer's disease. The daily dose was 20 to 30 mg of GM1 by intracerebroventricular infusion.

It was shown that 2x100 mg of free GM1 daily had a beneficial effect on the UPDRS of treated PD patients. The goal is to avoid daily-repeated injections because of the side effects they generate. In this trial the drug will be delivered i.v. as a weekly dose taking advantage of the longer circulation time of the liposomes. The known therapeutic dose, used in the study from Schneider *et. al.* in 2013, corresponds to a weekly exposure of 1400 mg of GM1. In China, for PD patients, the authorised dose is 80 mg daily (in addition to dopamine substitution therapy) resulting in 560 mg weekly GM1 administration. For TLN we expect a higher bioavailability due to the liposomal formulation. The starting dose is set to 6 mg TLN, which corresponds to 3% of the dose of GM1 that showed an effect when given s.c. and is less than 0.25% of the maximum that was ever applied i.v. at once (2500 mg). It is foreseen to increase the dose progressively to 12 and 60 mg then increasing by equal steps of 60 mg up to 720 mg. This planned maximum dose is 51% of the weekly exposure that was shown to be efficacious (s.c.) and 29% of the maximum dose injected at once (i.v.). Here a deliberately low dose was chosen to start with to ensure good tolerability at this level before incrementing the dose levels. At these doses and as a liposomal formulation we expect TLN to be efficacious, although the exposure is lower compared to that of the trial of Schneider *et. al.* in 2013. We moreover expect TLN to remain safe at these doses.

With the liposomal formulation of TLN there might be a more efficient blood brain barrier crossing and therefore more free-drug in the brain.

For the consolidation part, a 8 weeks treatment length has been selected since the UPDRS improvements have been described after 6 weeks in a previous study.

### 3.6 Explanation for choice of comparator (or placebo)

Not applicable

### 3.7 Risks / Benefits

According to the literature and non-clinical data of TLN, the profile of TLN is expected to be very safe. All components of TLN are metabolites that can be produced and broken down by the human body. There is very little risk of accumulation based on current knowledge. The known risks associated with GM1 from the literature are detailed in section **3.4.3 Clinical safety**. For the patients following the escalation schedule, the main risk is that TLN will be given for the first time in human as i.v. infusion. This is mitigated by a very low starting dose and a careful follow-up and escalation. The main risk potentially associated with TLN is an over performance compared with free GM1. Talineuren could reach the brain cells more efficiently than the free drug GM1 and might cause cerebral symptoms with disorientation, confusion, and headache similarly to what was observed in the trial using 50 mg intracranial injections on GM1. With a liposomal formulation i.v. injected by continuous infusion that could be stopped if encephalopathic side effects appeared, sudden local increase of GM1 (e.g., in the brain) will be avoided and therefore this risk is considered minimal.

There are also risks inherent to the weekly i.v. injections and the local pain caused by this repeated procedure over 8 or 14 weeks.

The potential benefit is a disease-modifying treatment that may slow down or even halt the progression of the disease by reduction of the neuronal decay, which could preserve functioning neurons and prevent symptoms from appearing or worsening. GM1 has been shown to increase neuronal survival and reduce neuroinflammation. This has been observed and documented *in vitro* and *in vivo*. First beneficial effects (in terms of UPDRS score reduction, with 6 points improvement) may be noticeable as early as after 6 weeks of treatment. The patients might clinically benefit from the drug even though this is only a phase I trial.

One potential risk identified is the potentially reduced need for levodopa in case that there was a significant therapeutic effect of TLN over the course of this trial. If the patients' condition improves the prescribed dose of levodopa might become too high. The levodopa treatment (or other similar medication) will then be continuously re-assessed during the trial by the PI and adjusted as clinically needed for the best care of the patient.

Although this is a safety trial and no potential benefits can be claimed to justify the risk for the patients, such a potential benefit does seem to be plausible (slowing of disease progression or even improvement) in this trial. However, the main benefit for the patients will be the participation in clinical research that may eventually improve the treatment of their condition.

### 3.8 Justification of choice of study population

In this phase I safety trial we wish to enrol PD patients only and do not plan the involvement of healthy volunteers.

The rationale for that is the following:

- 1- The API GM1 has been extensively used in humans over several years.
- 2- GM1 has already been administered to PD patients in other trials.
- 3- We expect a good safety profile, mainly because GM1 is a metabolite. The other compounds of TLN are also metabolites and should not present any safety issues.
- 4- The patients' current PD treatment (e.g., levodopa) will not be discontinued and therefore they will not miss out on any symptomatic treatment.
- 5- Lowered levels of GM1 have been shown in PD patients, therefore the risk of GM1 overdosing is lower in PD patients as compared to healthy volunteers.
- 6- TLN has not shown any sign of concern during extensive preclinical efficacy testing *in vivo*.
- 7- PD patients could potentially benefit significantly from the trial, hinting towards a better benefit/risk ratio in this population.

### **3.9 Justification for optional continued TLN infusions after the follow-up visit after the dose escalation part**

If patients experience a benefit on their condition from the study treatment, and since TLN will not be readily available as a medication at the conclusion of the patients' planned participation in the trial, InnoMedica wishes to give the patients extended access to the IMP in a safe and controlled manner. Based on the patient's wish, the three patients from dose escalation part will have the option to continue further with weekly TLN infusions after their follow-up visit up for an additional 8 weeks. This will allow the continuation of an eventual benefit from TLN for the patients whilst gathering further safety data on the IMP from repeated dosing.

## **4. STUDY OBJECTIVES**

### **4.1 Overall Objective**

The overall objective of this trial is to define the safety profile of TLN, to find a recommended dose for a phase II trial and validate the schedule of TLN administration in the described patient population. The aim is to ensure that TLN can be repeatedly administered safely to patients, in a weekly dose by i.v. route at a dose that is expected to produce a medical improvement of the patient's condition. The dose will be gradually increased until the targeted dose reaches to the corresponding weekly exposure that previously showed a beneficial clinical response for the free-drug GM1. Preliminary efficacy will be assessed at these different doses in order to later decide which dose might be recommended for further phase II trials.

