#### 6.1.1 Dose escalation (Part 1)

In this part a group of 3 patients will receive a single weekly dose that will be increased according to the schedule defined. In parallel, meaning that the first patient will receive a dose X on week Y, if the safety assessment is positive (see **Section 8.3 Dose modifications**) then the following week (Y+1) this patient will receive the next dose (X+1), on that week (Y+1) two other patients will receive the same dose X to confirm the safety assessment. *In fine*, every week patient 1 will receive one dose at the same time that patients 2 & 3 receive the preceding dose.

This weekly increase has been elected to allow rapid determination of the MSD and rapidly reach a dose level that will be beneficial for the patients involved in this trial. This is allowed by the fact that GM1 is expected to be safe and no clear AE are foreseen within this dose range. Furthermore, the 1 + 2 pattern allows one week observation of each dose increase in 1 patient before infusing 2 more.

The first dose level starts at 6 mg which will increase to 12 and 60 mg, then increasing by equal steps of 60 mg up to 720 mg. The escalation will be stopped individually according to the decision matrix detailed in the **Section 8.3 Doses modifications**. The three first steps of the dose are purposely low to account for any possible unexpected effects of the formulation.

Throughout the escalation part, all patients will be monitored twice weekly to record AEs and document them. Monitoring will take place once before each TLN infusion (beginning of the week) and a second time by the end of each week (performed by the principal investigator) to collect AE and allow enough time for the IMC to review them and take their decision on the next infusion/dose modification/delay.

At the end of the escalation, the average of the three maximum tolerated doses by the three patients will be defined as MSD for part 2. With this design, we aim to find the highest dose that generates, if any at all, at maximum only transient mild/moderate AEs. At the same time, this will allow to glean information on clinical effect for the planning of a potential phase II study.

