If a patient drops out for reasons unrelated to the drug treatment, this patient will be replaced. The three MSD are necessary to establish the dose that will be used for the multiple dose administration. This is a design that allows fast escalation with minimal risks for the patients since the dose steps are small, the starting dose is very low and each increment is split in a 1 + 2 pattern. With N=3 we expect to show evidence of common AEs inherent to the TLN formulation. This design (part 1) lacks the assessment of mid-term cumulative effects of the drug at a constant dosage. Therefore, an additional phase (part 2) will be performed to complete the safety profile under constant weekly dosages and provide more insight of the tolerability over 8 repeated doses.

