#### 6.1.3 Continued TLN infusions

Patients wishing to continue their treatment beyond the assessments in part 1 of the trial described above, can receive further weekly TLN infusions for up to 8 additional weeks at their personal MSD or at the dose level 14. A lighter schedule (one instead of two visits per week) than part 1 was elected for the patients' convenience. All patients will be monitored weekly to record AE and assessed based on details given in chapter **9. ASSESSMENTS**.

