#### Part 2 – Dose consolidation:

As soon as the MSD is defined, 9 patients will receive the full MSD in the multiple dose administration part once a week for 8 weeks.

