#### Part 1 – Dose escalation:

| Causality            | Intensity   | Resolution until next infusion | Next patient added/ Dose increase                                                                                                         |
|----------------------|-------------|--------------------------------|-------------------------------------------------------------------------------------------------------------------------------------------|
| (unlikely/unrelated) | grade 1 - 3 | yes/no                         | yes                                                                                                                                       |
| Possible             | grade 1     | yes                            | yes                                                                                                                                       |
| Possible             | grade 1     | no                             | yes                                                                                                                                       |
| Possible             | grade 2     | yes                            | yes                                                                                                                                       |
| Possible             | grade 2     | no                             | Delay till resolution (maximum of 3 weeks), then rechallenge at same dose level, if re-occurrence stop treatment for the affected patient |
| Possible             | grade 3     | yes/no                         | no (stop treatment for the affected patient but others to continue)                                                                       |
| Probable/definite    | grade 1     | yes/no                         | yes                                                                                                                                       |
| Probable/definite    | grade 2     | yes                            | yes                                                                                                                                       |
| Probable/definite    | grade 2     | no                             | no (stop treatment for the affected patient but others to continue)                                                                       |

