### 11.4 Planned Analyses

#### 11.4.1 Datasets to be analysed, analysis populations

Three main analysis populations will be employed

- **Safety Analysis Set:** all subjects who received at least part of a dose of the study medication
- **PK Analysis Sets:** subjects from the safety analysis set who provide sufficient data for the key PK evaluations and who do not violate any relevant selection criteria or have protocol violations affecting the assessment of PK.
- **Efficacy Analysis Set:** subjects from the safety analysis set who provide sufficient data for the key efficacy evaluations and who do not violate any relevant selection criteria or have protocol violations affecting efficacy assessments.

For all analyses, subjects will be grouped according to the cohort in which they were treated and/or the dosage they received. The composition of these analysis sets and the dose group or cohort will be finalized before DB lock for the primary who provide sufficient data for the key PK evaluations.

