#### 11.4.3 Secondary Analyses

Efficacy analyses will be conducted in the Efficacy Analysis Set. In addition to descriptive summaries of efficacy parameters over time by dose/cohort, for patients in the multiple dose part, a statistical comparison of the change from baseline to the last visit will be performed, e.g., by means of the Wilcoxon signed-rank test for continuous variables. The evolution over time will also be analysed: the choice for the specific model (e.g., mixed-models for repeated measures or random coefficients

models) will be made at the time of analysis-based considerations such as the distribution and timing of observations or missing data patterns.

PK analyses will be descriptive and PK parameters will be derived directly from the plasma concentration-time curves or calculated using non-compartmental methods.

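### Section 4.1 wants efficacy at the escalation doses to help choose the phase II dose, but in Part 1 dose level and week on treatment coincide and there is no control, so levels cannot be compared for efficacy

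*Protocol*

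**What the plan says.** Section 4.1 makes finding a phase II dose part of the overall objective and names efficacy as an input: "Preliminary efficacy will be assessed at these different doses in order to later decide which dose might be recommended for further phase II trials". Section 11.4.1 sets the grouping: "For all analyses, subjects will be grouped according to the cohort in which they were treated and/or the dosage they received". Section 11.4.3 plans "descriptive summaries of efficacy parameters over time by dose/cohort".

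The Part 1 schedule is in 6.1.1 and 8.1.1. Three patients receive one infusion a week at 6, 12 and 60 mg, then in steps of 60 mg up to 720 mg (14 levels). The patients are staggered: "every week patient 1 will receive one dose at the same time that patients 2 & 3 receive the preceding dose". The Part 1 table in 8.3 allows one departure from the weekly step, for an unresolved, possibly related grade 2 event: "Delay till resolution (maximum of 3 weeks), then rechallenge at same dose level".

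Constant dosing occurs in two places. In Part 2, "9 patients will receive the full MSD in the multiple dose administration part once a week for 8 weeks". In the optional prolongation (6.1.3), Part 1 patients "can receive further weekly TLN infusions for up to 8 additional weeks at their personal MSD or at the dose level 14". Section 6.1.1 concedes one limit: "This design (part 1) lacks the assessment of mid-term cumulative effects of the drug at a constant dosage". It offers Part 2 as the remedy, in terms of safety and tolerability. No section says that efficacy by level is confounded with time.

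**The concern.** A by-dose efficacy table from Part 1 will look like a dose-response, yet it can equally be a time course. Placebo response, practice, disease progression, delayed or cumulative drug effect and changes in Parkinson's medication (allowed in 8.3 and foreseen in 3.7) all run along the same axis as dose. LEDD is recorded, so medication changes will be visible, but they cannot be separated from dose either.

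The lag makes this sharper. Section 3.7 expects first benefit as early as after 6 weeks, and 3.5 uses that figure to set the length of Part 2. With weekly steps, an effect that takes this long would appear about six levels above the dose that started it.

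What is at stake is the efficacy part of the phase II dose argument. An improving trend would favour too high a dose and a worsening trend too low a dose.

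**Working it through.** The protocol gives no figure to reproduce here; 11.2 states that no formal calculation was made. The check is whether the schedule contains a dose contrast that is separate from time.

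**Inputs** (6.1.1, 8.1.1): doses d = 6, 12, 60, 120, …, 720 mg; own week on treatment w = 1, …, 14.

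**Planned ladder.** r = S_wd / √(S_ww × S_dd) = 13,155 / √(227.5 × 763,665) = 13,155 / 13,181 = 0.998. The rank correlation is 1.00, because level k is given in week k. A model holding both terms would have a variance inflation of 1/(1 − 0.9961) ≈ 256, so standard errors about 16 times larger. If escalation stops early, r is 0.972 (5 levels), 0.991 (8), 0.995 (10) or 0.997 (12).

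**Features that might break the alias:**

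- *Stagger.* It moves patients 2 and 3 by one calendar week. Own week on treatment is unchanged, so r stays at 0.998. Against calendar week, pooled over three patients, r = 0.991.
- *Delay and rechallenge.* Level j in week j, a delay of 1, 2 or 3 weeks, level j again, then one level per week, for each j from 1 to 14: within-patient Pearson 0.962 to 0.994, Spearman at least 0.999.
- *Prolongation, on-treatment infusions only.* Ladder to level L, then eight infusions at L in weeks L+5 to L+12 (assuming a start the week after the 4-week follow-up). L = 14: Pearson 0.92, Spearman 0.97. L = 8 (360 mg): 0.87 and 0.91. The added data lie at the patient's top dose and later in time.
- *Off-drug follow-up.* MDS-UPDRS and LEDD are taken 28 days after the last infusion (9.3.6) and again after prolongation (9.3.17). At the projected 30 h half-life (6.1.2), that is 28 × 24 / 30 = 22.4 half-lives. Entered as 0 mg, ladder plus follow-up gives 0.58 and 0.63 for L = 14; with prolongation and both follow-ups, 0.57 and 0.63 (L = 8: 0.46 and 0.52). These lower values come from contrasting the top dose with no drug, and assume a reversible effect without carry-over. The order of levels 1 to 14 against weeks 1 to 14 is unchanged.
- *Part 2.* One dose, so no dose contrast within it. Setting it against early Part 1 weeks compares nine patients with three different ones, non-randomised, and cannot rank the ladder.
- *Pre/post-infusion MDS-UPDRS Part III.* Readable within a visit as an immediate effect. Its trend across levels is still a trend across weeks.

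**Coverage.** At most 4 of the 14 levels can be held for several weeks: up to three personal maxima, plus the MSD if it falls on a level. At least 14 − 4 = 10 levels are given once per patient, apart from a rechallenge.

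**Lag, as an illustration.** If an effect takes 6 weeks to show and begins at level 3 (60 mg, week 3), it appears in week 3 + 6 = 9, at level 9 (420 mg).

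**The case against.** The strongest reply is that the protocol claims little. Section 4.1 calls the efficacy preliminary and says only that a dose might be recommended later. Section 11.1 states no hypothesis, and 6.1 and 11 make the analysis descriptive. Section 5.2 defines the MDS-UPDRS outcome as a course over time, the summaries in 11.4.3 carry a time axis, and the wording in 11.4.1 permits grouping by dosage without forcing it. The only significance test is confined to the multiple-dose part, and no dose-response model is planned. Confounding of this kind comes with within-patient escalation in three patients.

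All of that is true, and it limits the weight of the point. It does not remove it: 4.1 still names a comparison between doses as an input to the phase II choice, the schedule cannot supply that comparison, and nothing warns the reader.

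The off-drug visits also count for the other side. A score that improves up the ladder and is lost by day 28 would speak against pure drift, but would not show which level was responsible.

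A reader might infer that the trial will recommend too high a dose, or try to state how often the best-looking level would mislead. The documents support neither. They give no rule for picking a level on efficacy, no drift and no standard deviation, so any such rate would rest on invented inputs.

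**Conclusion.** The point holds and should be corrected, as a matter of what the trial may conclude rather than how it is run. In Part 1 a difference in efficacy between dose levels cannot be told from a difference between weeks on treatment (Pearson 0.998, Spearman 1.00 on the planned ladder). None of the protocol's other features separates one ladder level from another. This rests on the planned weekly escalation, with at most one delay per patient in the check.

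The size and direction of any resulting error cannot be derived from the documents. The 6-week lag is the protocol's own expectation, taken from an earlier study of free GM1 given subcutaneously; it may differ for this product.

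Two wider conclusions do not follow. The MSD, and so the Part 2 dose, is not distorted, because 6.1.1 and 9.2.2 compute it from the highest doses reached, without efficacy. The safety objective is not weakened by this point. Nor is Part 1 efficacy worthless: it can be described over time, with the day-28 visit as an off-drug reference.

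**What to change.** In 4.1, replace the last sentence with: *Efficacy in Part 1 will be described over time; because dose level and week on treatment coincide, differences between levels will not be read as dose-response or used on their own to choose between dose levels. The phase II dose will rest mainly on safety and tolerability, with efficacy and PK at the MSD from Part 2 as supportive single-dose information.*

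In 11.4.1 and 11.4.3, show Part 1 efficacy per patient by week on treatment, with dose and LEDD marked and the day-28 off-drug visit included. A by-level summary of the pre/post-infusion MDS-UPDRS Part III change may stay as an immediate effect, with the caveat that comparison across levels is confounded with week.

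A separate minor correction: the synopsis bases the MSD partly on efficacy, while the rule in 6.1.1 and 9.2.2 does not. The two should agree.

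The cost is wording and one changed display. No patient, visit, dose or sample changes. The sponsor gives up an efficacy argument for one escalation dose over another.
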